##### Depressive Symptoms

Depressive symptom severity was assessed with the Patient Health Questionnaire-9 (PHQ-9), a 9-item self-report measure aligned with the *DSM* (*Diagnostic and Statistical Manual of Mental Disorders*) symptom criteria and anchored to the preceding 2 weeks. Each item is scored 0 (“not at all”) to 3 (“nearly every day”), producing a total score from 0 to 27, where higher scores indicate more severe depressive symptoms. In Spanish primary care validation, the PHQ-9 showed strong internal consistency (reported as McDonald ω≈0.89) and good screening performance for major depressive disorder, with high sensitivity and moderate specificity depending on the selected cut-point and reference standard [37].

##### Anxiety Symptoms

Anxiety symptom severity was measured with the Generalized Anxiety Disorder-7, a 7-item self-report scale also anchored to the preceding 2 weeks, using the same 0-3 response options and yielding a total score from 0 to 21; higher scores indicate more severe anxiety. The Spanish adaptation demonstrated excellent internal consistency (α≈0.94) and strong short-term stability (test-retest ICC≈0.84), alongside evidence of concurrent validity through strong correlations with established anxiety and disability measures [38].

##### Post–COVID-19 Functional Status Scale

Functional limitations were assessed using the Post–COVID-19 Functional Status Scale (PCFS), administered as a self-completed web-based questionnaire (REDCap). The PCFS is an ordinal measure grading limitations from 0 (no functional limitations) to 4 (severe functional limitations), with higher grades indicating greater restriction in usual activities and lifestyle. Because PCFS is an ordinal functional status grade rather than a multi-item psychometric scale, internal consistency is not applicable; instead, measurement quality is supported by agreement and construct validity [39]. The Spanish web-based PCFS has demonstrated substantial test-retest reliability (κ=0.63) and high agreement between web- and paper-based formats (88% agreement), alongside strong construct validity through expected correlations with health status and activity limitation measures (eg, EQ-5D-5L questionnaire and Global Activity Limitation Indicator) [40].

##### Cognitive Performance

Cognitive domains relevant to attention/executive control, processing speed, and visuoconstructive memory were assessed with standardized neuropsychological tests. Selective attention and inhibitory control were assessed using the Stroop Color and Word Test, generating condition scores and an interference index reflecting executive control under competing stimulus demands [41]. Processing speed and attention were assessed with the Symbol Digit Modalities Test, which measures rapid visual scanning, sustained attention, and speeded substitution under timed conditions [42]. Visuoconstruction and visual memory were evaluated using the Rey-Osterrieth Complex Figure, including copy accuracy and recall performance using standardized scoring procedures [43]. These instruments have extensive normative use in clinical and experimental contexts, and standardized administration enhances reliability across assessment waves.

##### Pain Catastrophizing

Maladaptive pain-related cognition was measured with the Pain Catastrophizing Scale (PCS), a 13-item measure covering rumination, magnification, and helplessness. Items are typically rated on a 0-4 scale and summed to a total score from 0 to 52, where higher scores reflect greater catastrophizing. The original PCS demonstrated robust psychometric development and validation [44], and the Spanish version has shown excellent internal consistency (α≈.94) and strong test-retest reliability (ICC≈0.88), supporting its use in Spanish-speaking clinical populations [45].

##### Fatigue Severity

Fatigue was assessed using the Fatigue Severity Scale (FSS), a 9-item questionnaire capturing the impact and severity of fatigue on daily functioning. Responses are typically scored from 1 to 7 and summarized as a mean score (commonly interpreted with higher values indicating greater fatigue severity) [46]. In post–COVID-19 recovery clinic populations, the FSS showed excellent internal consistency (α≈0.96) and expected construct validity through correlations with quality of life and depressive symptoms, supporting its use for quantifying clinically relevant fatigue in this context [47].

#### Biochemical and Immunological Markers

Fasting venous blood samples will be collected at baseline (T0) and follow-up (T1) to characterize participants’ biochemical, hematological, coagulation, inflammatory, and immunological profiles. All measurements will be performed in the routine hospital clinical laboratory according to standard operating procedures. Standard panels will include basic biochemistry, a complete blood count, and a coagulation profile. Systemic inflammation will be assessed using circulating inflammatory markers, including CRP and IL-6, and broader immune signatures will be characterized through cytokine profiling using a predefined panel. Humoral response to SARS-CoV-2 will be assessed using quantitative antispike immunoglobulin G serology, recorded as a continuous measure. Potential viral reactivation will be explored by measuring serological markers for latent herpesviruses, including EBV, cytomegalovirus, and HSV-1. Biomarker variables will be analyzed as candidate correlates of persistent symptoms and as longitudinal measures to evaluate change between T0 and T1.

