### Appointments and Procedures

Data collection will be organized into 2 study appointments. During the first appointment, fasting blood samples will be collected for routine laboratory analyses, and participants will sign informed consent covering both study participation and biobank sample storage. Participants will also receive standardized instructions for completing the self-administered questionnaires online through REDCap [31]. The second appointment will include completion of exploratory tests and the collection of any additional clinical or sociodemographic data not captured at the first visit. Standardized procedures will be used at each visit to minimize measurement variability and ensure comparability across participants and across time points. The participant flow and assessment schedule are summarized in Figure 1.

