### Variables and Measurements

#### Overview

Study variables will include outcomes related to persistent symptoms and functioning, additional patient-reported outcomes, cognitive performance measures, and laboratory biomarkers, alongside core sociodemographic and clinical covariates. Measurements will be obtained at T0 (baseline) and repeated at T1 (follow-up) using the same instruments and procedures to support longitudinal comparisons. Textbox 1 summarizes the study variables collected for sociodemographic, clinical, lifestyle, psychological/functional, and biological domains.

Study variables.

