#### Lifestyle and Psychosocial Variables

##### Overview

All participant-reported outcomes will be collected at the baseline visit (T0) and repeated at the follow-up visit (T1; ~3 years after T0) using the same administration procedures. Self-administered questionnaires were completed in a standardized order, with staff available to resolve comprehension issues without coaching responses. Neurocognitive tests were administered by trained personnel following published manuals and standardized instructions. A detailed summary of instruments, scoring, recall periods, and key measurement properties is provided in Multimedia Appendix 1 [32-47].

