##### Objective 3: Evaluate Symptom and Outcome Evolution From T0 to T1

Longitudinal changes in continuous secondary outcomes (eg, questionnaire scores, cognitive test metrics, and selected continuous biomarkers) will be modeled using mixed-effects models including fixed effects for group (case vs control), time (T0 vs T1), and the group × time interaction to estimate differential change over time, with random intercepts for participants and appropriate correlation structures. Binary/ordinal outcomes will use generalized mixed-effects models with appropriate links (logit for binary; ordinal models for ordered scales where applicable). Primary longitudinal contrasts will be (1) within-group change and (2) between-group difference in change (interaction term), each reported with 95% CIs.

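### Within-group T0–T1 change in laboratory biomarkers cannot be distinguished from a between-wave assay shift; the group × time contrast should carry the inference

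*Protocol article*

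**What the plan says.** Under Biochemical and Immunological Markers, fasting blood is drawn at both waves for routine panels, CRP and IL-6, a cytokine panel, antispike IgG and herpesvirus serologies. The section states that "All measurements will be performed in the routine hospital clinical laboratory according to standard operating procedures", and that biomarkers serve partly "as longitudinal measures to evaluate change between T0 and T1".

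The interval appears in the Overview of Lifestyle and Psychosocial Variables, where participant-reported outcomes are "repeated at the follow-up visit (T1; ~3 years after T0) using the same administration procedures". Blood belongs to the same T0 and T1 waves. The Overview of Variables and Measurements adds that measurements are "repeated at T1 (follow-up) using the same instruments and procedures to support longitudinal comparisons".

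Objective 3 of the Statistical Analysis fits mixed models with group, time (T0 vs T1) and their interaction to continuous secondary outcomes, with these examples: "questionnaire scores, cognitive test metrics, and selected continuous biomarkers". It then sets the contrasts for all of them alike: "Primary longitudinal contrasts will be (1) within-group change and (2) between-group difference in change (interaction term), each reported with 95% CIs".

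The laboratory data check described under Objective 1 looks at individual extreme values and laboratory flags. The listed sensitivity analyses cover matching, collinearity, transformations and cohort type, but not assay date or period.

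**The concern.** A questionnaire that is unchanged in wording and scoring has no counterpart to a reagent lot or a calibrator. An assay does. If calibration moves between waves, T1 values move together by a modest amount. No single value then looks extreme, so a check on outliers and flags would not pick it up. In the planned model this movement goes into the time coefficient, and the within-group contrast is built from that coefficient.

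At stake are statements that a marker rose or fell over about 3 years in Long COVID, where the within-group estimate is the natural one to quote. More recruitment would not help: a systematic shift does not shrink with n, while the standard error does. False discovery rate control addresses chance findings, not bias.

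**Working it through.** **The plan's own figure.** The plan gives no figure on assay stability. Its one computed figure, the sample size, does reproduce. With proportions 0.20 and 0.365 (mean 0.2825), two-sided α = 0.05 and 90% power:

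n = [1.960·√(2·0.2825·0.7175) + 1.282·√(0.20·0.80 + 0.365·0.635)]² / 0.165² ≈ 154.4, or 155 per group.

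This point does not depend on it.

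**Inputs.**
- From the article: 100 participants per group enrolled as of February 2026 (Recruitment and Follow-up Progress). The target of about 400 means about 200 per group if split equally. Tests are two-sided, with α = 0.05 in the sample size section.
- Assumed, because the documents give no values: no true change, equal SD at both waves, T0–T1 correlation r of 0.5 or 0.7, no attrition, and an assay shift of δ SD that is additive on the analysis scale.

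**Within-group change.** In SD units, SE = √(2(1−r)/n). The chance of p < 0.05, or equally of a 95% CI that excludes zero, is Φ(δ/SE − 1.96) + Φ(−δ/SE − 1.96).

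- r = 0.5, n = 100: SE = √(1.0/100) = 0.100. With δ = 0.2, δ/SE = 2.00 and the chance is 51.6%.
- r = 0.7, n = 100: SE = √(0.6/100) = 0.0775. With δ = 0.2, δ/SE = 2.58 and the chance is 73.3%.

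| Chance of a significant within-group change, r = 0.5 to 0.7 | δ = 0 | δ = 0.1 | δ = 0.2 | δ = 0.3 |
|---|---|---|---|---|
| n = 100 per group | 5% | 17–25% | 52–73% | 85–97% |
| n = 200 per group | 5% | 29–45% | 81–96% | 99–100% |

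On a log scale, a 10% calibration change is ln(1.10)/0.5 = 0.19 SD if the log SD is 0.5. A 20% change is ln(1.20)/1.0 = 0.18 SD if the log SD is 1.0. Both SDs are assumed.

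**Group × time interaction.** SE = √(2(1−r))·√(2/n). A shift common to both groups cancels from the difference in change, so the error rate stays at 5%. A multiplicative shift cancels in the same way after log transformation. If half of the shift differs between groups, the bias is δ/2. For δ = 0.2, r = 0.5 and n = 100, that is 0.1/0.1414 = 0.71 SE, which gives 10.9%. With r = 0.7 it gives 15.0%.

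**The case against.** The strongest reply is that the article already contains the remedy. Recovered controls are assayed at both waves and the interaction is the other primary longitudinal contrast. A common shift would show as parallel change in the two groups with an interaction near zero. This stands, and it rules out saying that nothing in the plan could reveal drift. Parallel change could still be a real secular change, however, and Objective 3 gives the within-group contrast equal rank for assays.

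A reader might also infer more than the documents support:
- That drift will occur and be reported as biology. No drift is documented. The article promises standard operating procedures and the same procedures at both waves, and it interprets results as associations. Those promises do not say that lots, calibrators or platforms stay constant.
- That wave and assay period coincide completely. Enrolment is staggered: T0 began in late 2022/early 2023, 200 of about 400 had been enrolled by February 2026, and T1 in late 2025/early 2026 is for the earliest participants. Later T0 samples may share a period with early T1 samples. The article also does not say when the cytokine panel is run. The confounding may therefore be partial, but a T0/T1 time term makes no use of that.
- That the study's main result is affected. The primary analysis is case status by conditional logistic regression. Within-group change is primary only inside a secondary objective, whose statement names symptoms and patient-reported outcomes. Biomarkers enter through the Objective 3 analysis and the biomarker section.
- That missing lot control, batching or bridging is a defect. Such detail may sit in the full protocol, which is not shown.

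Finally, the percentages describe one marker at an unadjusted 5% level under a supposed shift. They are not an estimate of actual risk, and false discovery rate adjustment may lower them without removing the bias.

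**Conclusion.** The point holds as a limit on interpretation that one sentence can repair. On the stated model, within-group change in a laboratory biomarker cannot be separated from a between-wave assay shift, so it should not be an inferential contrast of equal rank with the interaction. Under the assumptions above, a common shift of 0.2 SD raises a nominal 5% error to 52–73% at 100 per group, while the interaction stays at 5%. Whether any shift exists is unknown.

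The interaction's protection is good but incomplete. It depends on the shift being common to both groups, and sampling or assay date is not a matching variable. Questionnaire and cognitive outcomes are outside this point.

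**What to change.** In Objective 3, add a sentence for laboratory biomarkers only. It should say that the between-group difference in change is the inferential longitudinal contrast. Within-group change is then reported descriptively with its 95% CI, beside the change in the control group, with a note that it may include assay shift. The interaction is already planned, so no new data or model is needed. The cost is the loss of a formal within-group biomarker test. The article places primary analyses after T1 is complete, so the sentence can be added before them.

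A sensitivity analysis that adds assay date or assay period to the biomarker models is also reasonable, because enrolment is staggered and groups may meet a shift at different times. It will be informative only to the extent that T0 and T1 assays overlap in calendar time.

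Running T0 and T1 cytokines together is optional and the fix does not depend on it. The article says that "participants will sign informed consent covering both study participation and biobank sample storage", but it does not establish that paired aliquots exist or that re-assay is permitted and funded. T0 aliquots would also have been stored longer than T1 aliquots.

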### Statistical Analysis

#### Overview

All analyses will be performed using IBM SPSS Statistics (version 27) and R software (R Foundation for Statistical Computing). Statistical inference will emphasize effect sizes with 95% CIs and clinically interpretable magnitudes; 2-sided tests will be used. Given the observational design, analyses will be interpreted as associations rather than causal effects. For interpretability, candidate “differential factors” will be grouped by temporality: (1) antecedent factors (eg, sociodemographic and preinfection comorbidities), (2) periacute factors (eg, markers of acute COVID-19 severity such as hospitalization/ICU admission and related clinical features), and (3) concurrent correlates measured at baseline in the postacute phase (eg, patient-reported outcome measures and biomarkers at T0). Antecedent and periacute factors will be interpreted as candidate determinants, whereas concurrent measures will be interpreted primarily as phenotypic correlates differentiating Long COVID from recovered controls.

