**Sociodemographic**
Age, sex/gender, place of residence, occupation, education level, and ethnicity

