#### Sociodemographic and Clinical Variables

Key sociodemographic variables will include age, sex/gender, place of residence, occupation, education, and ethnicity. Clinical history related to the acute SARS-CoV-2 infection will include onset date, acute symptoms, hospitalization, and intensive care unit (ICU) admission (if applicable), and the method used for diagnostic confirmation. Preexisting and incident comorbidities will be recorded, including (but not limited to) cardiovascular disease, diabetes, chronic respiratory disorders, and other relevant conditions, to support confounding control and stratified analyses.

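### Occupation and place of residence are collected at T0 with no pre-infection reference date, yet fall in the group read as candidate determinants of Long COVID

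*Protocol article*

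**What the plan says.** The Statistical Analysis overview forms three groups by timing. The first is "antecedent factors (eg, sociodemographic and preinfection comorbidities"; the second holds features of the acute episode; the third is "concurrent correlates measured at baseline in the postacute phase (eg, patient-reported outcome measures and biomarkers at T0". The reading attached to the first two is fixed: "Antecedent and periacute factors will be interpreted as candidate determinants". The third group is read mainly as phenotypic correlates. The Hypothesis and Rationale section makes the same split. The overview also says that "analyses will be interpreted as associations rather than causal effects".

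Textbox 1 lists the sociodemographic items as "Age, sex/gender, place of residence, occupation, education level, and ethnicity". The section on sociodemographic and clinical variables repeats the list without a reference date: "Key sociodemographic variables will include age, sex/gender, place of residence, occupation, education, and ethnicity".

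On timing, the Variables and Measurements overview counts the core sociodemographic covariates among the study variables and states: "Measurements will be obtained at T0 (baseline) and repeated at T1 (follow-up) using the same instruments and procedures". Appointments and Procedures gives the second appointment the task of "collection of any additional clinical or sociodemographic data not captured at the first visit".

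**The concern.** Sorting by timing is the plan's own safeguard against mistaking a consequence of Long COVID for a precursor. It works only if everything in the antecedent group describes the participant before or at infection. In the overview the qualifier *preinfection* attaches to comorbidities alone, and the sociodemographic domain is admitted unqualified.

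For age, sex/gender and ethnicity this does no harm, and for education little. Occupation and place of residence are different: a person with Long COVID may change job, stop working or move because of the illness. If the T0 value is used, the exposure is measured after the outcome and is then read as a candidate determinant.

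The error would be differential. Recovered controls are defined by having no persistent or new symptoms, so they cannot change work because of Long COVID, although they can change it for other reasons. Matching on sex, age and diagnosis date does not remove such an error, and neither does a larger sample. Associations with sociodemographic factors are part of the primary objective, so its interpretation is affected.

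**Working it through.** **Order of events, from the article**

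| Step | Section | Timing |
|---|---|---|
| Infection, retrospective cohort | Study Design | early stages of the pandemic |
| Case status reached | Eligibility Criteria | symptoms for at least 12 weeks after onset |
| T0 begins | Timeline and Data Collection Milestones | late 2022/early 2023 |
| Occupation and residence collected | Variables and Measurements; Appointments and Procedures | T0 appointments, repeated at T1 |

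Every case is past 12 weeks at T0. If the early stages are taken as 2020 (an assumption), T0 began about 2 to 3 years after infection for the retrospective cohort. The split between retrospective and prospective participants is not given, and the lag is probably shorter for prospective ones.

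**Which items are affected.** Six are listed. Sex/gender is matched exactly and age within 3 years. Ethnicity is fixed and education mostly so in adults. That leaves occupation and residence.

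**Where the T0 values belong.** The third group is defined by measurement at baseline in the postacute phase. T0 values of occupation and residence meet that definition, but the first group claims them by domain. The two definitions overlap, and they carry different interpretations.

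**Benchmark from the plan.** The sample size section uses 20% prevalence in controls and an odds ratio of 2.3.
- Case odds = 2.3 × 0.20/0.80 = 0.575; case prevalence = 0.575/1.575 = 0.365. This agrees with the stated 36.5%.
- The usual formula for two independent proportions (two-sided 0.05, 90% power, no continuity correction) gives 155 per group, as stated. The sample size is not in dispute; it supplies a scale for the illustration.

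**Illustration.** Assumptions, none of them from the article: a binary status such as not working; prevalence 20% in both groups before infection; true odds ratio 1.0; a share s of unexposed cases becomes exposed by T0; no control changes.

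Case prevalence at T0: q = 0.20 + 0.80 × s. Odds ratio = [q/(1 − q)] / (0.20/0.80).

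| s | q | Odds ratio |
|---|---|---|
| 5% | 0.24 | 1.26 |
| 10% | 0.28 | 1.56 |
| 15% | 0.32 | 1.88 |
| 20% | 0.36 | 2.25 |

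Reaching 2.3 needs s = (0.365 − 0.20)/0.80 = 20.6%.

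**If controls change too.** With 10% of unexposed cases and 5% of unexposed controls changing, the prevalences are 0.20 + 0.80 × 0.10 = 0.28 and 0.20 + 0.80 × 0.05 = 0.24. The odds ratio is (0.28/0.72)/(0.24/0.76) = 1.23, against 1.56 when no control changes.

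These are unpaired odds ratios, in line with the plan's sample size method; the primary model is conditional logistic regression.

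**The case against.** The strongest reply is that the article says when data are collected, not what period each item refers to. Preexisting comorbidities and acute-episode features are also gathered by a study that begins at T0, and they refer to earlier dates. The data collection form and the original protocol (Multimedia Appendix 2) are not shown and may ask for occupation at infection. This stands as a limit: that the T0 value is what gets recorded is inferred. It does not dispose of the point, because the article does anchor comorbidities and acute features in time and leaves these items unanchored, while the sorting rule and its interpretation are stated outright.

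It can also be said that the bracketed entries are only examples and that T0 occupation would fall in the third group by its definition. That is the sensible reading, but the text names the sociodemographic domain under the first group and no such item under the third. Nor are occupation and residence named in the core adjustment set or the example blocks, so their place in the models is not fixed.

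A reader might go further and infer that the study will report consequences of Long COVID as its causes. The article does not support that: it disclaims causal effects, calls its aim hypothesis-generating and speaks of candidate determinants. The disclaimer still does not repair the sorting, which separates determinants from correlates and puts these two items on the wrong side if they hold T0 values.

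The illustration is also fairly criticised. It uses employment status, whereas the article lists occupation, and someone on leave may report the same occupation. The rates are assumed, and letting controls change shrinks the result.

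**Conclusion.** The point holds for occupation and place of residence, and marginally for education. It does not extend to the whole sociodemographic domain. As the article is written, post-infection values of these items can be presented as candidate determinants of Long COVID status.

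The size cannot be established from the article. The range of 1.26 to 2.25 rests on 20% prevalence before infection, no true association, and change in 5% to 20% of unexposed cases only. A reader might infer from its upper end that a spurious effect near the plan's 2.3 is to be expected. The documents give no rate of change for either group, and modest change among controls brings the figure down to values such as 1.23. What follows is that the error can run from negligible to material, and that the present wording does not guard against it.

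The conclusion assumes that no unseen form already asks for the value at infection. If one does, a clause saying so settles the matter. No sample size figure is affected.

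**What to change.** In the Statistical Analysis overview, limit the antecedent group to fixed characteristics and to values that applied at the date of the acute infection. State that occupation and place of residence recorded as status at T0 are treated as concurrent correlates. Bring the Hypothesis and Rationale section into line.

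Where occupation and residence at infection can be obtained, use those values in the antecedent group: from health records where available, or by asking at T0 those still to be enrolled. As of February 2026, 200 of about 400 planned participants had been enrolled, so this remains possible for roughly half the target.

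The reclassification costs one sentence; the additional items cost a line or two on the form. Asking enrolled participants at T1 is optional. It relies on recall several years back, which may differ between cases and controls, and it may come too late for the earliest enrolled, whose T1 was scheduled for late 2025/early 2026. If no infection-date value can be had, the reclassification alone still removes the mislabelling.
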